#### Statistical analyses

The focus of the primary analyses will be on the comparisons between the two interventions for each of the primary outcome (HAM-A and PSWQ-A) follow-up measurements. Each co-primary outcome will be tested at the two-sided, 0.025 significance level (i.e. using a Bonferroni adjustment). Comparisons of outcome measures (or transformations thereof) between intervention groups will be made by mixed-model repeated measures analysis of covariance with an unstructured covariance matrix to account for the fact that multiple measurements (at approximately 2 months post-randomization, 4 months post-randomization, 9 months post-randomization, and 15 months post-randomization) from participants are not independent. Each primary hypothesis will be tested at the 4-month visit using a contrast within the framework of this mixed-effects, repeated measures analysis. In the primary analysis, all randomized subjects will be included in their original study group regardless of the final mode of intervention or the extent of compliance with the study protocol; that is, the primary analysis will follow an “intent to treat” philosophy. The analysis of covariance model for the primary outcomes will contain terms for the baseline value of the outcome, therapist (a factor to which participants are randomized), baseline current depressive disorder (used to stratify randomization), use of psychotropic medications at baseline (used to stratify randomization), the intervention effect, a time effect, and the time by intervention interaction term. The interaction term is necessary in the model to allow the test of the primary hypothesis on the 4-month post-intervention measurement. Additional secondary analyses will be performed to test between intervention groups for measurements at approximately 2 months post-randomization, 9 months post-randomization, and 15 months post-randomization. We will also perform a test of interaction between the therapist and intervention effect to explore if the therapist effect moderates the effect of the intervention.

Secondary outcomes, including the BDI-II, PAT-D, SF-36, and ISI will be analyzed using mixed models repeated measures analysis of covariance using techniques like those described for the primary outcomes. We will perform hypothesis tests at the 0.05 level for these outcomes and following the recommendations of Wang et al. [42], we will report the overall probability of Type I error within published manuscripts.

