### Aims and hypotheses

The primary aim of this study is to compare the efficacy of telephone-delivered cognitive-behavioral therapy (CBT-T) with nondirective supportive therapy (NST-T; an active comparison condition) for reducing anxiety and worry. We hypothesize that CBT-T will be superior to NST-T in reducing anxiety and worry. Our secondary hypotheses are that CBT-T will be superior to NST-T in improving coexistent symptoms (depressive symptoms and sleep) and functional status (disability and quality of life). The hypotheses will be tested on outcome measures assessed immediately upon completion of the intervention (i.e., the 4-month post-randomization visit).

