#### Sample size calculation

We used data from a pilot study trial comparing CBT-T with usual care with referral for reducing anxiety and worry in older adults with anxiety disorders (N = 55; n = 29 in usual care with referral and n = 26 in CBT-T) [14] to determine the sample size for the current study. Analyses of these pilot data provided estimates of the standard deviation (SD) for the Penn State Worry Questionnaire-A (PSWQ-A) and Hamilton Anxiety Rating Scale (HAM-A) scores: values were 6.7 and 7.2, respectively. The correlation between baseline and post-intervention PSWQ-A scores was 0.45 for the PSWQ-A and 0.40 for the HAM-A. We considered a 0.5 SD difference on the PSWQ-A (3.35 units) and the HAM-A (3.5 units) in the post-intervention means as the minimally important detectable difference. A mixed effects analysis appropriate for repeated measures analysis of covariance will be used to test the primary hypotheses, with a contrast to test the hypothesis of no intervention effect at the post-randomization visit. Using the pilot data estimates of SD and correlation and assuming that each co-primary outcome will be tested at the 0.025 two-sided significance level, power calculations for analysis of covariance on the PSWQ-A outcome indicated the need for a total of 80 participants per group to attain 90% power, 70 participants per group to provide 85% power, and 60 participants per group to attain 78% power. We plan to recruit 88 participants per group to account for an expected drop-out rate of approximately 10%.

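### Testing both co-primary outcomes by plain Bonferroni gives up power that Holm's step-down procedure recovers under the same 0.05 familywise bound

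*Protocol article*

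**What the plan says.** Under Statistical analyses, the protocol article names HAM-A and PSWQ-A as the two primary outcomes. It tests each by one contrast at the 4-month visit and sets the level: "Each co-primary outcome will be tested at the two-sided, 0.025 significance level (i.e. using a Bonferroni adjustment"). The Sample size calculation section uses the same level: "assuming that each co-primary outcome will be tested at the 0.025 two-sided significance level". The article describes no step-down rule or reallocation of alpha, and gives no reason for preferring the single-step rule.

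The hypothesis under Aims and hypotheses covers both outcomes: "We hypothesize that CBT-T will be superior to NST-T in reducing anxiety and worry".

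The planning inputs are under Sample size calculation. The SDs are "HAM-A) scores: values were 6.7 and 7.2, respectively" (PSWQ-A first). On the correlations it says "The correlation between baseline and post-intervention PSWQ-A scores was 0.45 for the PSWQ-A and 0.40 for the HAM-A", and on the target differences "We considered a 0.5 SD difference on the PSWQ-A (3.35 units) and the HAM-A (3.5 units) in the post-intervention means". Power is stated for PSWQ-A only: "80 participants per group to attain 90% power, 70 participants per group to provide 85% power", and "60 participants per group to attain 78% power".

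**The concern.** Under the plan each outcome is held at 0.025 whatever the other one shows. Suppose PSWQ-A gives p = 0.001 and HAM-A gives p = 0.03. The plan must call the anxiety result non-significant. Holm compares 0.001 with 0.025, rejects, then compares 0.03 with 0.05 and rejects again, with the same guarantee on the familywise error.

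The second rejection matters in this trial because the investigators want to claim benefit on anxiety as well as on worry. HAM-A is also the outcome with the lower power under the plan's inputs, and the article states no power for it. Holm helps most on that outcome and on the joint result.

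**Working it through.** **Inputs** (Sample size calculation): SD 6.7 (PSWQ-A) and 7.2 (HAM-A); baseline to post-intervention correlation 0.45 and 0.40; differences 3.35 and 3.5 units; 80 evaluable per group; two-sided 0.025 per outcome. The correlation between the two test statistics is not given, so it is assumed and varied from 0 to 0.9.

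**Step 1: reproduce the plan's figures.** The analysis-of-covariance residual SD is SD × √(1 − r²).
- PSWQ-A: 6.7 × √(1 − 0.45²) = 5.983
- HAM-A: 7.2 × √(1 − 0.40²) = 6.599

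The expected test statistic is difference / (residual SD × √(2/n)). At n = 80:
- PSWQ-A: 3.35 / 0.946 = 3.541
- HAM-A: 3.5 / 1.043 = 3.354

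With critical value 2.241 (two-sided 0.025), power for PSWQ-A is Φ(3.541 − 2.241) = 90.3%. The same formula gives 85.8% at 70 and 79.5% at 60 per group. The noncentral t gives 89.8%, 85.1% and 78.6%. The plan states 90%, 85% and 78%, so its figures reproduce. For HAM-A at 80 per group, which the article does not report, Φ(3.354 − 2.241) = 86.7%.

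**Step 2: the Holm rule.** An outcome is rejected if its statistic exceeds 2.241, or if it exceeds 1.960 and the other exceeds 2.241. Both are rejected if both exceed 1.960 and at least one exceeds 2.241. Writing P and H for the two statistics:

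Power on both = Pr(P > 2.241, H > 1.960) + Pr(P > 1.960, H > 2.241) − Pr(P > 2.241, H > 2.241)

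Check at correlation 0, where the probabilities multiply. Pr(P > 1.960) = Φ(1.581) = 0.9431 and Pr(H > 1.960) = Φ(1.395) = 0.9184.
- Bonferroni: 0.9031 × 0.8672 = 0.783
- Holm: 0.9031 × 0.9184 + 0.9431 × 0.8672 − 0.9031 × 0.8672 = 0.829 + 0.818 − 0.783 = 0.864

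**Step 3: results at 80 per group** (bivariate normal). Bonferroni power is 90.3% for PSWQ-A and 86.7% for HAM-A at every correlation.

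| Assumed correlation | PSWQ-A, Holm | HAM-A, Holm | Both, Bonferroni | Both, Holm |
|---|---|---|---|---|
| 0 | 93.8% | 91.4% | 78.3% | 86.4% |
| 0.3 | 93.4% | 91.0% | 79.7% | 87.0% |
| 0.5 | 93.0% | 90.7% | 80.9% | 87.6% |
| 0.7 | 92.6% | 90.4% | 82.5% | 88.4% |
| 0.9 | 91.7% | 90.1% | 84.8% | 89.5% |

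Critical values from t with 157 degrees of freedom lower each figure by less than one point and leave the gains essentially as they are.

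**Step 4: error rates** (4 million simulated pairs). With both nulls true, the familywise error is the same under either rule, 3.6% to 4.9% across correlations 0.9 to 0. With only HAM-A null, it is 2.5% under Bonferroni and 3.9% to 4.7% under Holm. All are within 0.05.

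**The case against.** The strongest reply is that nothing here is wrong. Bonferroni controls the error, is prespecified and agrees with the sample size calculation. The one power target in the article, 90% for PSWQ-A, is met. The article sets no target for success on both outcomes. All of that stands, and it is why this is an improvement and not a correction.

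Other limits also stand:
- The probability of success on at least one outcome does not move (92.2% to 98.7% across correlations 0.9 to 0, under both rules).
- The gain on one outcome depends on the other being effective. With no HAM-A effect, PSWQ-A gains only about 0.1 point.
- Only the 0.05 bound is shared. Part of the gain comes from using alpha that Bonferroni leaves unspent when one null is true.
- HAM-A power is calculated at the stated 3.5 units, while 0.5 × 7.2 = 3.6. At 3.6 units Bonferroni gives 88.7%, and Holm at correlation 0.5 gives 92.1%, so the gain is a little smaller.
- Bonferroni has 97.5% simultaneous intervals that always agree with its tests. Under Holm, HAM-A at p = 0.03 would be rejected while its 97.5% interval includes zero. This is a real cost, though the article commits to no simultaneous intervals.

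One further argument is that a claim requiring benefit on both outcomes would need no adjustment at all, since each could be tested at 0.05. That is correct for such a claim. But the plan tests two separate hypotheses and allows success on either, and for that structure Holm is the right comparison.

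**Conclusion.** The concern holds as a worthwhile, low-cost improvement to a valid plan. Holm can never lose a rejection that the current rule would make, and it keeps the familywise error at or below 0.05 whatever the correlation. If both effects are as planned and 80 per group are evaluable, it adds 3.4 to 4.6 points of power on HAM-A and about 1.4 to 3.5 points on PSWQ-A. For success on both it adds 4.7 to 8.1 points, or 6.7 points at correlation 0.5. These sizes rest on the pilot SDs and correlations, the planned differences and the assumed range of between-outcome correlation. That Holm is at least as powerful rests on none of them.

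**What to change.** In Statistical analyses, replace the Bonferroni sentence with: *The two primary hypotheses will be tested by the Holm procedure at an overall two-sided level of 0.05. The smaller p-value is compared with 0.025 and, if it is significant, the other is compared with 0.05.*

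Add a line saying that the Holm decision governs significance, and that 97.5% intervals will be reported for both outcomes although the interval for the outcome tested second may include zero when Holm rejects. The Sample size calculation can remain at 0.025, described as conservative.

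The cost is this wording, settled before unblinding. It needs no extra participants, data or modelling. The one thing given up is automatic agreement between each test and its 97.5% interval.

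### The repeated-measures model gives baseline one slope for all four visits; a baseline-by-time term is a cheap improvement for the 9- and 15-month contrasts and leaves the primary 4-month test essentially unchanged

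*Protocol article*

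**What the plan says.** All of the following stands in the Statistical analyses section of the protocol article, except where noted.

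- The method is "mixed-model repeated measures analysis of covariance with an unstructured covariance matrix", fitted to the measurements "at approximately 2 months post-randomization, 4 months post-randomization, 9 months post-randomization, and 15 months post-randomization".
- The mean model is given term by term. It starts "The analysis of covariance model for the primary outcomes will contain terms for the baseline value of the outcome", continues with therapist and the two stratification factors, and ends with "the intervention effect, a time effect, and the time by intervention interaction term". The time-by-intervention term is the only interaction listed for this model.
- On the primary test: "Each primary hypothesis will be tested at the 4-month visit using a contrast".
- On the other visits: "Additional secondary analyses will be performed to test between intervention groups for measurements at approximately 2 months post-randomization", and likewise at 9 and 15 months.
- The BDI-II, PAT-D, SF-36 and ISI are to be analysed by similar techniques.
- The Sample size calculation section gives one correlation between baseline and post-intervention scores per outcome (0.45 for the PSWQ-A, 0.40 for the HAM-A). It gives none for the 2-, 9- or 15-month visits.

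**The concern.** Only the intervention effect may change from visit to visit. The baseline score is assumed to predict the 2-month score and the 15-month score with the same slope. The unstructured covariance lets variances and correlations differ freely across visits, so the mean model is stricter than the covariance model, and the article gives no reason for that.

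A score usually predicts a measurement two months away better than one fifteen months away. If that holds here, a common slope is a compromise that fits the late visits worst. Two things are then at stake at 9 and 15 months. The first is precision, because part of the baseline information is lost. The second is bias when participants drop out, because a wrong slope adjusts wrongly for any baseline difference between the participants who remain in each arm.

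**Working it through.** **Inputs from the article.** SDs for PSWQ-A and HAM-A: "values were 6.7 and 7.2, respectively". Correlation of baseline with post-intervention PSWQ-A: 0.45. Target difference: 3.35 units (0.5 SD). Level: "assuming that each co-primary outcome will be tested at the 0.025 two-sided significance level". Stated sizes: 80, 70 and 60 per group for 90%, 85% and 78% power. Expected dropout: about 10%. The Background reports attrition of up to 33% in earlier studies.

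**Assumed inputs.** The baseline correlations at 2, 9 and 15 months and the correlations among follow-up visits are not in the article. The ranges used are shown below.

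**1. Reproduce the plan's figure.** The residual SD is 6.7 × √(1 − 0.45²) = 5.98. Then n per group = 2 × (2.2414 + 1.2816)² × (1 − 0.45²) / 0.5² = 79.2, or 80. Power by noncentral t at 80, 70 and 60 per group is 89.8%, 85.1% and 78.6%. The stated figures hold.

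**2. Variance at each visit.** Work in SD units, with baseline correlation r_t at visit t.
- With baseline-by-time, the adjusted variance is proportional to 1 − r_t².
- With one slope b, it is proportional to (1 − r_t²) + (r_t − b)².
- The common slope settles at b = (1ᵀS⁻¹r) / (1ᵀS⁻¹1), where S = R − rrᵀ and R is the correlation matrix of the follow-up visits.

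Example: r = 0.55/0.45/0.35/0.25 and follow-up correlation 0.6 give b = 0.457. At 15 months the variance excess is (0.25 − 0.457)² / (1 − 0.25²) = 0.0429 / 0.9375 = 4.6%, so the SE excess is 2.3%.

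**3. SE excess of the common-slope model** (complete data, follow-up correlation 0.6):

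| Baseline correlation at 2/4/9/15 months | 2 mo | 4 mo | 9 mo | 15 mo |
|---|---|---|---|---|
| 0.45 throughout | 0% | 0% | 0% | 0% |
| 0.50/0.45/0.40/0.35 (mild) | 0.3% | 0.0% | 0.1% | 0.5% |
| 0.55/0.45/0.35/0.25 (moderate) | 0.6% | 0.0% | 0.7% | 2.3% |
| 0.60/0.45/0.30/0.15 (steep) | 0.5% | 0.3% | 2.7% | 6.8% |

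With follow-up correlation 0.5, or autoregressive at 0.7, the 15-month excess is 0.4% (mild), 1.7 to 2.0% (moderate) and 4.3 to 5.5% (steep).

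**4. Power for 0.5 SD, 80 per group, two-sided 0.025, follow-up correlation 0.6** (normal approximation, common slope against by-time).
- At 15 months: 86.9 against 87.2% (mild), 83.0 against 84.7% (moderate), 77.4 against 83.1% (steep).
- At 4 months: 90.3% both ways in the first two patterns, 90.1 against 90.3% in the steep one.

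**5. Dropout** (simulated mixed models, N = 176, SD units).
- *Constant slopes, dropout of 10 to 33% unrelated to baseline.* The extra term raises the SE by about 0.1 to 0.25%.
- *Constant slopes, 33% dropout depending on baseline differently by arm.* The extra term raises the SE by 1/0.9742 − 1 = 2.6% at 9 months and 1/0.9513 − 1 = 5.1% at 15 months. Neither model is biased.
- *Moderate weakening, the same dropout.* The common-slope model is biased by 0.08 SD at 9 months and 0.17 SD at 15 months; a separate recomputation gave about 0.13 SD at 15 months. The by-time model is close to unbiased, with an SE about 1.5 to 2% larger. Against the 0.5 SD target, 0.13 to 0.17 SD is about a quarter to a third.

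**The case against.** The strongest reply is that a single baseline slope in a mixed-model analysis of covariance is a valid specification. Under randomization with complete data its contrasts are unbiased. The article tests its primary hypotheses at 4 months, where nothing practical changes. The premise that the slope weakens is general experience, not something the article shows. A condensed article may also leave further model terms to an analysis plan.

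Most of this stands, and it sets the size of the point. The last argument is weaker. The article does not leave the mean model open: it names each term and explains why its one interaction is needed. The comment is therefore on a stated choice. For the secondary outcomes the article only points to similar techniques, so there the restriction is carried over by implication.

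A reader might infer three stronger things that the documents do not support.
- *That the term is free.* It is not quite. With constant slopes and heavy dropout tied to baseline and arm, it costs about 5% of the 15-month SE.
- *That the gain is large.* An 8% gain at 15 months can be produced by assuming a fall in correlation from 0.70 to 0.15, but nothing in the article supports so steep a fall.
- *That the term always sharpens the later contrasts.* In the dropout case with weakening slopes its benefit is the removal of bias, and the SE is slightly larger.

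**Conclusion.** The point holds as a cheap improvement to planned secondary contrasts. As listed, the model has one baseline slope for all visits. If the slope weakens, freeing it cuts the 15-month SE by about 0.5 to 2% (mild to moderate) or 4 to 7% (steep), and the 9-month SE by about 0.1 to 3%. It also protects both contrasts from bias when dropout depends on baseline differently by arm. If the slope is constant there is no gain.

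It would be wrong to conclude that the primary analysis or the sample size is flawed. The 4-month SE changes by 0.3% or less in the patterns tabulated. Only an extreme pattern, with the correlation falling to zero by 15 months (0.60/0.45/0.20/0.00), exceeds that: 0.03 to 2.8%, depending on the follow-up correlation. The stated 80 per group reproduces.

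The sizes rest on assumed correlations at 2, 9 and 15 months and among follow-up visits. The bias figures also rest on a deliberate stress case of 33% dropout, well above the roughly 10% that the trial expects.

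**What to change.** Add a baseline-by-time interaction to the prespecified repeated-measures model for the HAM-A and PSWQ-A, and to the secondary-outcome models of the same type. A constrained longitudinal model, with baseline as part of the outcome vector, achieves the same. The 4-month contrast remains the primary test, and the sample size needs no change.

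The cost is one line in the plan and three parameters per outcome (four visit-specific slopes in place of one) with 176 participants. Under ordinary dropout that is about 0.1 to 0.25% of the SE when slopes are constant. The worst case found is the 5% at 15 months described above. The term should be fixed before the outcome data are compared by arm, so that the choice of slope cannot depend on the result.

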## Discussion

In this RCT, we compare telephone-delivered CBT with NST as a treatment for Generalized Anxiety Disorder in rural older adults. We hypothesize that CBT-T will be superior to NST-T in reducing anxiety and worry. We also hypothesize that CBT-T will be superior in reducing depressive symptoms and sleep problems, and improving functional status.

We have chosen NST as a comparison condition because it provides a structurally equivalent comparison group [43] and has similar levels of outcome expectations and credibility [23,44] as CBT. We have designed the interventions such that all participants get the same number and length of sessions. Thus, NST as a comparison group allows for the demonstration of the superiority of CBT to a structurally equivalent comparison. It also provides all participants with an opportunity to receive treatment.

### Implications for practice

Telephone-delivered psychotherapy is one method of providing treatment to individuals limited by practical barriers. This method may be particularly appropriate for older adults living in rural settings as they are less likely to have access to the internet [45]. Further, patient satisfaction with telephone delivered psychotherapy is high and comparable to face-to-face psychotherapy [14]. Should we demonstrate the efficacy of the CBT-T intervention over NST-T, this low-cost treatment could be implemented widely and could potentially reach large numbers of patients in rural areas, primary care settings, and specialty settings, or in circumstances when older adults have barriers to seeking care.

## Abbreviations

BDI-II: Beck depression inventory; CBT-T: Cognitive behavioral therapy-telephone; GAD: Generalized anxiety disorder; HAM-A: Hamilton anxiety rating scale; ISI: Insomnia severity index; NST-T: Nondirective supportive therapy-telephone; PAT-D: Pepper assessment tool for disability; PSWQ-A: Penn state worry questionnaire-abbreviated; SCID: Structured clinical interview for the dsm-IV; SD: Standard deviation.
